### Outcomes

#### Primary Outcome Measure

The primary outcome is the children's pathology according to the [(Caregiver-) Teacher Report Form (C-)TRF, caregiver/teacher version of the Child Behavior Checklist] score between baseline 2 (T2) and post treatment (T3) as well as between T2 and the 6-month follow-up (T4) after end of treatment (37, 38) as the literature shows that mentally ill parents can be biased in rating their children's symptoms (39). Further, teacher ratings have been shown to demonstrate greater predictive validity in the long term ratings (40). In comparison to shorter questionnaires [e.g., Strengths and Difficulties Questionnaire (SDQ) (41)], the CBCL also produces more variance. As the CBCL is used in various studies as a primary outcome measure (15), we will be able to compare our data to a broad range of other results. Further outcome measures are mental disorders according to the Diagnostic Interview of Mental Disorders for parents and children (DIPS and Kinder-DIPS) (42–44) respectively for children under the age of 6 years the Structured Interview for Preschool Ages (SIVA) (45) and the parent rating of the children's pathology according to the CBCL (for detailed descriptions see below). Thus, we will be able to validate the teacher ratings with the Kinder-DIPS diagnoses and can compare the concordance of the teacher and parent ratings.

#### Secondary Outcome Measures

Children's and parents dimensional severity index of a broad range of mental disorders according to the DSM-5 based clinical interview (Kinder-)DIPS (42–44) respectively the SIVA (45), parent's psychopathology according to the Brief Symptom Inventory (BSI) (46), personality traits (PID-5-BF) (47), children's psychopathology according to the CBCL-parentversion (37, 38), parenting skills (EFB) (48), parental stress (ESF) (49), children's and parents knowledge about mental disorders [semistructured interview adapted from Beardslee and Röhrle, (50)], direct medical costs and direct and indirect non-medical costs (TiC-P) (51), health-related quality of life in parents [EuroQoL/EQ-5D-5L, AQoL-8D (52, 53)], health-related quality of life in children (KIDSCREEN-10) (54, 55) (for details see Table 1).

**Table 1 T1:** List of diagnostic domains and measurements.

	**Who?**	**Where?**	**T1**	**T2**	**Intermediate**	**T3**	**T4**
Eligibility screening	Family	Local	x				
Socio-demographics	Parents	Local	x				
Structured clinical interview with the patient (DIPS)	Patient	Local	x	x		x	x
Structured clinical interview for children (Kinder-DIPS/SIVA)	Parent	Local	x	x		x	x
Brief Symptom Inventory (BSI)	Parents	Online	x	x	x (patient)	x	x
Personality traits (PID-5-BF)	Parents	Online	x	x		x	x
Child Behavior Checklist (CBCL)	Parents	Online	x	x		x	x
(Caregiver-) Teacher Report Form [(C-)TRF, caregiver/teacher version of the CBCL]	Teacher	Online	x	x		x	x
Parenting Skills (EFB)	Parents	Online	x	x		x	x
Parental Stress (ESF)	Parents	Online	x	x		x	x
Knowledge about mental disorders	Parents, children	Local	x	x		x	x
Direct and indirect costs in children and parents (adapted TiC-P)	Parents	Online	x	x		x	x
Health-related quality of life in parents (EuroQoL/EQ-5D-5L, AQoL-8D)	Parents	Online	x	x		x	x
Health-related quality of life in children (KIDSCREEN-10)	Parents, children (>8)	Online	x	x		x	x
(Serious) adverse events	Parents, children	Local		x	x (patient)	x	x
Psychopharmaka and other drugs	Parents, children	Local	x	x	x	x	x
Concomitant interventions	Parents, children	Local	x	x	x	x	x

### Instruments

The (Kinder-) DIPS is a diagnostic interview for mental disorders and is available for the diagnoses of mental disorders from age 6 to adulthood according to ICD-10 and DSM-5. The SIVA is a diagnostic interview for mental disorders for preschool ages according to ICD-10 and DC: 0–5. A translation table to DSM-5 diagnoses has been created for this study. For parents we use the DIPS; for their children the Kinder-DIPS or SIVA. Conducting the interviews with the patient takes around 60–90 min as well as the child assessment with the Kinder-DIPS or SIVA for each child. Different studies have shown good quality criteria for these interviews (43, 45).

The Achenbach System of Empirically Based Assessment (ASEBA) (56) consists amongst others of questionnaires for preschool (C-TRF and CBCL 1,5-5, consisting each of 100 problem items) and school-ages (TRF and CBCL, consisting each of 113 problem items). Answers are rated on a three point Likert-scale (0 = Not true to 2 = Very True or Often True) and can be scored on different subscales, the second order scales internalizing problems and externalizing problems as well as on a total problem scale. Studies have reported good to very good internal consistency with *r* > 0.86 for the second order scales and the total problem scale of the preschool age-versions (37) and Cronbach's alpha >0.80 for the second order scales and at least.93 for the total problem scale in the school age-versions (38). In the current study we use the parent (CBCL) and teacher (TRF) ratings of the ASEBA.

The Brief Symptom Inventory (BSI) is a self-report questionnaire consisting of 53 items that are rated on a five point Likert-scale (0 = not at all to 4 = very much). Answers are scored on nine Primary Symptom Dimensions and three Global Indices. Internal consistency with Cronbach's alpha > 0.70 for the subscales and > 0.90 for the Global Indicee GSI is good to very good (46).

The Personality Inventory for DSM-5-Brief Form (PID-5-BF) is a self-report questionnaire assessing 5 personality traits (negative affect, detachment, antagonism, disinhibition, and psychoticism). The 25 items are rated on a 4 point Likert-scale (0 = very false or often false to 3 = very true or often true). An average score for each domain and an overall score can be calculated with higher scores indicating greater dysfunction. The average domain and overall personality dysfunction scores were found to be reliable in the DSM-5 Field Trials (47).

The Elternstressfragebogen (ESF) is a German self-report questionnaire with 38 items assessing parental stress. The answers are rated on the four scales Parental Stress, Role Restriction, Social Support, and Partnership. The internal consistency is good with Cronbach's alpha > 0.76 (49).

The Erziehungsfragebogen (EFB) is the German adaptation of the English Parenting Scale (57). The self-report questionnaire consists of 35 items and can be rated on the scales Overreactivion, Laxness, and Verbosity as well as on a total score. The internal consistencies of the scales Overreaction, Laxness, and the total score is acceptable to good with Cronbach's alpha > 0.74. For Verbosity the internal consistency is lower with Cronbach's alpha > 0.59 (48).

To assess knowledge about mental disorders, a semi structured interview was adapted from Beardslee and Röhrle (50). Domains of the interview are knowledge about mental disorders in general, knowledge about the primary diagnosis of the mentally ill parent, causes of the mental illness, coping with the mental illness and communication. Conducting the interviews separately with all family members over the age of 6 years takes 15 min each.

The questionnaire on healthcare consumption and productivity losses for patients with a Psychiatric disorder (TiC-P) is a comprehensive and widely used self-report questionnaire focusing on establishing direct medical costs and indirect costs (e.g., productivity losses due to absenteeism and presenteeism) (51). The TiC-P is a feasible and reliable instrument for collecting data on medical consumption and productivity losses in patients with common mental health conditions (58). The TiC-P has been previously adapted for use in Germany (59). For this study, we adapted the TiC-P for use in children.

The EQ-5D-5L is a widely used instrument to calculate quality-adjusted life years (QALYs) (52). The EQ-5D-5L comprises 5 items covering 5 domains (mobility, self-care, usual activities, pain/discomfort, and anxiety/depression), each of which is rated as causing “no problems,” “slight problems,” “moderate problems,” “severe problems,” and “extreme problems.” Theoretically, the EQ-5D-5L generates 3,125 different health states. Preference-based utilities for each of these health states are available for Germany with “full health” and “death” being anchored at 1 and 0, respectively (60).

The Assessment of Quality of Life (AQoL) instruments are health-related multi-attribute utility quality of life instruments. The AQoL is a reliable and valid instrument (53). The AQoL-8D consists of five psycho-social and three physical dimensions. With one exception (dimension “senses”), each of these represents a psychometrically valid sub-scale [e.g., tests indicate they measure a common construct (61)]. Utility scores were obtained by a four-stage methodology (62).

The KIDSCREEN-10 index consists of 10 items each answered on a 5-point Likert scale. The index provides a good discriminatory power along the health-related quality of life trait-continuum. The KIDSCREEN-10 Index shows good psychometric properties (63). Utility scores will be derived by an algorithm for mapping the KIDSCREEN-10 index onto the CHU9D utility scores, a preference-based instrument developed specifically for application in cost-utility analyses (54).

### Sample Size

The sample size calculation is based on the primary outcome measure (change in TRF score between T2 and T3) which is hierarchically ranked on top of the multiple testing procedure. Based on the results described above (14, 15, 64), it is assumed that the standardized treatment effect for this outcome expressed by Cohen's d amounts to d = 0.25. With a two-sided significance level of α = 0.05 and a power of 1–β = 0.8 using a two-sample *t*-test, 253 patients per group (*n* = 506 in total) are required. Since the primary outcome is measured on the child level and it is possible to enroll multiple children per patient, a hierarchical multi-level model with patients at level 1 and children at level 2 will be fitted. Taking a drop-out rate of 20 % into account, *n* = 634 patients need to be enrolled into the trial in the analysis. This attrition rate is conservative and based on results from the longitudinal STAR^*^D study that also carried out long-term follow-up assessments (13), as well as on other studies in the field that report even lower attrition rates (65, 66). The problem of attrition and missing values will also be addressed in the analysis by applying the intention-to-treat principle. For missing values, imputation techniques will be applied, thus partly resolving this problem. Since it is assumed that parts of the outcome variance can be explained by the inclusion of covariates, the actual power of the analysis by a linear multi-level model is expected to be higher than 1–β = 0.8. Assuming that the number of children enrolled per patient amounts to 1.5, we expect that *n* = 950 children will participate in the trial. The enrollment of more than one child per patient is expected to yield an additionally increased power. Sample size calculation was performed using SAS v9.4 (SAS Institute, Cary, NC).

### Randomization

Patients will be assigned in a 1:1 ratio to either the control intervention (CBT) or the experimental intervention (CBT+Triple P) through a centralized web-based tool (www.randomizer.at). Randomization will be performed stratified by center, comorbidity (yes/no), and total number of children (1/more than 1). To achieve equal group sizes per stratum block randomization will be performed. The block length will be defined by the study biometrician and treated confidentially to prevent selection bias.

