The study will be conducted at eight university outpatient clinics throughout Germany: Bielefeld, Bochum, Gießen, Landau, Leipzig, Mainz, Marburg, and Munich. All cooperating sites have established outpatient clinics for research and teaching as well as psychotherapy training institutes and are well-known specialized treatment centers for psychotherapy. The patients are primarily recruited from the university outpatient clinics at each study site. The study centers have continuous experience in conducting psychotherapy studies with recruitment of large patients numbers (30, 31). The patients to be recruited per center and fulfilling all inclusion criteria will be attainable over a 15-month acquisition period at all study sites without the need to change the existing infrastructure. If possible, all children between 1.5 and 16 years of age (at T1) and a partner living together with the family shall be included in the study. A legal guardian not living together with a child can upon request be offered to participate in the study and to complete questionnaires about the respective child. Inclusion only takes place if the family participates voluntarily in the study. There is no compensation for study participation.

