### Statistical Methods

Our primary efficacy analysis will be based on the full analysis set (FAS) according to the intention-to-treat (ITT) principle, reflecting the recommendations given in relevant guidelines (67). The FAS is defined to include all patients enrolled who are assigned to the treatment group they were originally randomized to, regardless of whether they actually underwent the assigned treatment or not. This will be the primary population for evaluating all efficacy endpoints and subject characteristics. Additionally, the per-protocol (PP) population, including all FAS patients with no major protocol deviations, will serve as a secondary analysis population and be used for sensitivity analyses. Before lock of the database, each patient's allocation to the FAS or PP population will be defined in the statistical analysis plan.

The two hypotheses to be assessed in the primary efficacy analysis are ordered hierarchically: In the first step, the null hypothesis ${\text{H}}_{0}^{\text{I}}$: $\mu_{\text{CBT}+\text{PPP}}^{\text{T}3-\text{T}2}$ = $\mu_{\text{CBT}}^{\text{T}3-\text{T}2}$ for the primary outcome “change in teacher CBCL (Teacher Report Form/TRF) score between T2 and T3” is tested at the two-sided significance level of 5% against the alternative ${\text{H}}_{1}^{\text{I}}$: $\mu_{\text{CBT}+\text{PPP}}^{\text{T}3-\text{T}2}$ ≠ $\mu_{\text{CBT}}^{\text{T}3-\text{T}2}$. If ${\text{H}}_{0}^{\text{I}}$ can be rejected, the null hypothesis ${\text{H}}_{0}^{\text{II}}$: $\mu_{\text{CBT}+\text{PPP}}^{\text{T}4-\text{T}2}$ = $\mu_{\text{CBT}}^{\text{T}4-\text{T}2}$ for the second primary endpoint “change in TRF score between T2 and T4” is tested at the two-sided level of 5% against its alternative ${\text{H}}_{1}^{\text{II}}$: $\mu_{\text{CBT}+\text{PPP}}^{\text{T}4-\text{T}2}$ ≠ $\mu_{\text{CBT}}^{\text{T}4-\text{T}2}$. Application of this multiple test procedure for a priori ordered hypotheses ensures control of the family-wise type I error rate at a level of 5%. The null hypotheses will be assessed using a linear mixed multi-level model with patients at level 1 and children at level 2, adjusting for center, number of comorbidities, number of children, baseline TRF score at T2, and length of waiting period between T1 and T2 (in weeks).

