Data missing for the primary outcome variable will be replaced by using multiple imputation (68) which takes the covariates treatment group, center, number of comorbidities, number of children, baseline TRF score at T2, and length of waiting period between T1 and T2 (in weeks) into account by applying the fully conditional specification method (69). This will be realized using the option “FCS” of the SAS “MI” procedure implemented in SAS 9.4. Sensitivity analyses will be performed by applying alternative methods dealing with missing data such as complete case analysis. All secondary outcomes will be evaluated descriptively, and descriptive *p*-values are reported together with 95% confidence intervals for the corresponding effects. Further exploratory analyses will be performed to identify potential prognostic factors (e.g., parental disorder, child psychopathology, socio-economic status) and mediators (e.g., Brief Symptom Inventory/BSI, Parenting Questionnaire/EFB, Parental Stress Inventory/ESF) for an intervention effect. The safety analysis includes calculation of frequencies and rates of adverse and serious adverse events together with 95% confidence intervals. All analyses will be performed with SAS version 9.4 or higher.

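### Randomisation stratifies on comorbidity yes/no and on one versus more than one child, but the primary and imputation models name the number of each; the randomised factors should be added alongside.

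*Protocol article*

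**What the plan says.** The Randomization section of the protocol article gives three stratification factors: "Randomization will be performed stratified by center, comorbidity (yes/no), and total number of children (1/more than 1". Allocation is 1:1, and blocks are used within strata: "To achieve equal group sizes per stratum block randomization will be performed". The Participants section gives the number of centers: "The study will be conducted at eight university outpatient clinics throughout Germany". That makes 8 × 2 × 2 = 32 strata.

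The Statistical Methods section sets the covariates for both primary tests (change from T2 to T3, then from T2 to T4): "adjusting for center, number of comorbidities, number of children, baseline TRF score at T2", plus the length of the waiting period. Multiple imputation repeats the list with treatment group added; it "takes the covariates treatment group, center, number of comorbidities, number of children, baseline TRF score at T2" and the waiting period into account.

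The article gives no reason why the covariates take a different form from the stratification factors.

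**The concern.** Blocking within strata balances the arms on the yes/no comorbidity factor and on one versus more than one child. A model-based standard error reflects that balance in full only if the model can represent those factors. A linear term in a count does so only as far as the outcome follows a straight line in the count. If the real contrast is between none and any, part of the variance removed by design stays in the residual.

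The list governs a trial described as confirmatory, covers both primary tests and carries over into the imputation model. The Sample Size section also relies on covariates to lift power above 0.80. The stake is slight: precision, and agreement between design and analysis.

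**Working it through.** **1. Comparing the two sections**

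| Factor | Randomization | Primary and imputation models |
|---|---|---|
| Center | center | center (match) |
| Comorbidity | yes/no | number (mismatch) |
| Children | total number, 1 or more than 1 | number (count or category not stated) |

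**2. The plan's own figure.** Inputs from the Sample Size section: d = 0.25, power 0.80, "two-sided significance level of α = 0.05", 20% dropout. The exact two-sample t-test needs 252.13 per group, so 253 (power 0.801), 506 in total. Dropout: 253 / 0.8 = 316.25, so 317 per group and 634 in total. The plan's figures reproduce, and they do not depend on how the covariates are coded.

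**3. Simulation.** From the document: 506 patients, 8 centers, 1:1 blocked allocation in 32 strata, d = 0.25. Assumed, because the document gives no values:
- blocks of 4
- 0 to 4 comorbidities with probabilities 0.35, 0.30, 0.20, 0.10, 0.05
- 1 to 4 children with probabilities 0.60, 0.28, 0.09, 0.03
- the two variables together explain R² = 2%, 5% or 10% of outcome variance, in equal parts

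Clustering of children and baseline TRF were left out. Each scenario had 4,000 runs. All models contain treatment and center; they differ in using linear counts, the randomised factors, or both. Mean standard error and power at d = 0.25:

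| True relation | R² | SE counts | SE factors | SE both | Power counts / factors / both |
|---|---|---|---|---|---|
| Step | 2% | 0.0884 | 0.0880 | 0.0882 | 80.8 / 81.2 / 81.1% |
| Step | 5% | 0.0876 | 0.0868 | 0.0869 | 81.3 / 81.4 / 81.3% |
| Step | 10% | 0.0860 | 0.0844 | 0.0846 | 83.4 / 84.7 / 84.8% |
| Linear in count | 2% | 0.0880 | 0.0883 | 0.0882 | 81.4 / 81.0 / 81.1% |
| Linear in count | 5% | 0.0868 | 0.0875 | 0.0869 | 81.3 / 80.6 / 81.3% |
| Linear in count | 10% | 0.0845 | 0.0860 | 0.0846 | 83.7 / 82.9 / 83.5% |

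At R² = 10%: with a step, 0.0860 / 0.0844 = 1.019, so counts are 1.9% worse. With a linear relation, 0.0845 / 0.0860 = 0.983, so counts are 1.7% better. The model with both is at worst 0.0846 / 0.0844 = 1.002 or 0.0882 / 0.0880 = 1.002 times the better one.

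**4. Why the result is symmetric.** Under the assumed distributions, the squared correlation between a count and its own dichotomy is
- comorbidity: 0.42² / (1.36 × 0.2275) = 0.570
- children: 0.33² / (0.6075 × 0.24) = 0.747

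The mean is 0.659. Whichever coding is wrong captures 0.659 of R². The expected ratio of standard errors is √[(1 − 0.659 R²) / (1 − R²)], which is 1.003, 1.009 and 1.019 for R² = 2%, 5% and 10%. This agrees with the simulation up to rounding.

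**5. Type I error.** Across the six null scenarios: counts 4.7% to 5.9%, randomised factors 4.8% to 5.9%. The Monte Carlo standard error is √(0.05 × 0.95 / 4000) = 0.34 percentage points. The highest values, 5.9% for each coding, come from the same simulated data sets, so they do not separate the two.

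**The case against.** Several counter-arguments have force.

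- Only comorbidity clearly changes form. The Randomization section itself gives the dichotomised children factor a name containing the word number, so the model's covariate may be that same factor.
- Linear entry of the counts is inferred. The article calls the model linear, which describes the model class and not the coding of covariates. If the number of comorbidities entered as categories with none as its own level, the yes/no contrast would already be in the model. Such coding is commonly settled in a SAP, which is not shown.
- A count determines its stratum and carries more information. A reader might infer that the plan loses precision or errs on the conservative side; this holds only if the effect is a step, and the document does not say which relation applies. Simply replacing the counts could cost precision.
- The model adjusts for baseline TRF, which may already absorb much of any comorbidity effect, so R² = 10% may be generous.
- The covariates are named in advance and identically for analysis and imputation, so the text does not support a charge that it invites a choice after the data are seen.

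All of this limits the claim. It does not remove the difference in wording for comorbidity, and it does not count against adding the randomised factors.

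**Conclusion.** The point holds as a minor one. As written, comorbidity does not enter the primary or imputation model in its randomised form, and the children covariate can be read two ways. If the counts enter linearly, the standard error lies between about 2% larger and about 2% smaller than with the randomised factors, depending on an unknown true relation. The largest power difference seen was 1.3 percentage points (84.7% versus 83.4%). These sizes rest on the assumed distributions, R² of at most 10%, and a simulation without clustering or baseline TRF.

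A reader might go further and conclude that the analysis disregards the stratification or that the primary tests are invalid. The documents do not support that: center is in the model, the other two factors are represented at least in a related form, type I error was about the same under both codings, and 253 per group and 634 enrolled stand.

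**What to change.** In the Statistical Methods section and the SAP, state that the primary model and the imputation model both include the stratification factors as randomised: center, comorbidity (yes/no) and one versus more than one child. Keep the number of comorbidities and the number of children as additional covariates, and state how they are coded. Do not swap the counts for the binary factors, since that loses a little if the outcome follows the count.

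The cost is a line of text and two degrees of freedom, or one if the children covariate already means the dichotomy. The overlap between a count and its dichotomy affects only their own coefficients, which are not of interest; the standard error of the treatment effect stayed within about 0.3% of the better coding in every scenario.
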